#### Follow up assessment (T3)

Three months after entering the TC, all intervention and control group participants are asked to complete a follow up interview, which includes qualitative questions relating to their time spent at the TC. In instances where a client does not enter the TC, the T3 is administered six months after the baseline assessment. For a list of measures used in the T3 assessment, see Table 1.

### Measures

Assessment information for this study was drawn from semi-structured clinical interviews and self-report questionnaires. In addition clinicians trained in mental health assessment administered standardised questionnaires and clinical assessment tools. A list of measures used at each assessment point is provided in Table 1.

### Clinician administered measures

#### Demographic questionnaire

A basic demographic questionnaire was used to capture client characteristics and included questions relating to age, education, socio-economic status as well as personal and familial history of substance use and mental health issues.

#### Mini International Neuropsychiatric Interview

The MINI [57] is a short, structured diagnostic interview, used to diagnose depression, anxiety, psychotic and substance use disorders from DSM-IV criteria. It takes approximately 15 minutes to administer and uses a decision logic tree to assess the major Axis I disorders in the DSM-IV-TR and ICD-10. The MINI is reported to demonstrate high reliability and good concordance with other diagnostic measures such as the Composite International Diagnostic Interview and Structured Clinical Interview DSM-III-R-Patients [57,58]. The MINI was administered at T1 to clinically assess all potential diagnoses identified from the MINI-Screen. All participants are administered the sections assessing social anxiety disorder, antisocial personality disorder, alcohol use and substance use disorder. The social anxiety, alcohol use and substance use disorder sections of the MINI are also administered at T3.

#### Alcohol, Smoking and Substances Involvement Screening Test (ASSIST)

The ASSIST [59] is a reliable and valid screening test for problematic or risky substance use. Eight questions assess cannabis, cocaine, amphetamines, inhalants, sedatives, hallucinogens, opiates and other miscellaneous drugs, alcohol and tobacco use within the context of a more general health and lifestyle-screening interview. Australian research indicates that it is a valid screening test for substance use in individuals who use a number of substances and have varying degrees of substance use [60].

#### Timeline Follow-Back method (TLFB)

The TLFB [61] measure was used to determine quantity and frequency of alcohol and drug use. The TLFB is an established calendar-based assessment tool created to assist client recall of substance consumption over a desired time period using date-based memory triggers. Use in the previous 90 days was recorded.

### Self-report measures

#### Liebowitz Social Anxiety Scale (LSAS)

The LSAS [54] is a 24 item scale assessing levels of fear and avoidance across a range of social and performance interaction situations. Items are rated on a four point scale, with higher scores indicative of more severe social anxiety. SAD is determined by an empirically-derived cut-off score e.g., [29,62]. The LSAS has been found to possess acceptable psychometric properties [63], and has been found to be sensitive to changes in social anxiety following treatment. Although originally used as a clinician administered scale, research has shown the self-report version to be equivalent [64].

#### Beck Anxiety Inventory (BAI)

The BAI [65] is a 21- item measure of the severity of anxiety in psychiatric populations. Participants rate the severity of each symptom of anxiety on a 4-point Likert scale (0 = not at all, to 3 = severely - I could barely stand it). Items are summed for a total score. The BAI demonstrates good internal consistency, test-retest reliability and convergent validity with Hamilton Anxiety Rating Scale–Revised (Beck et al., [65]).

#### Beck Depression Inventory-II (BDI)

The BDI [66] consists of 21 items measuring common symptoms of depression on a 4-point Likert scale (0 = not at all, to 3 = severely - I could barely stand it). Items are summed for a total score. The BDI demonstrates high internal consistency, test-retest reliability and convergent validity with the Hamilton Rating Scale for Depression–Revised [67]

#### Circumstances, Motivation and Readiness for Treatment Scale (CMRS)

The CMRS is a 20 item scale [68] developed as a self-report scale of client perceptions across four interrelated domains: circumstances (external pressure), motivation (intrinsic pressure), readiness and suitability for residential treatment. Scale items are rated on a 5-point likert scale from 1 (Strongly Disagree) to 5 (Strongly Agree) with the option to select N/A if the question does not apply to the respondent. The CMRS was found to have acceptable internal consistency (.87 for the total scale), and was found to be predictive of treatment durations of longer than 30 days.

#### Client Satisfaction Questionnaire-8 (CSQ-8)

The CSQ-8 [69] is an 8-item questionnaire designed to measure client satisfaction with a particular health-care service, and was used to evaluate how satisfied the clients were with the social anxiety intervention. The CSQ-8 has good internal reliability, ranging from .83 to .93; while high construct validity has also been demonstrated [69]. The CSQ-8 has been translated into 15 different languages, and is utilised across a wide range of populations and health services [69].

### Qualitative questions

In addition to the structured measures, qualitative questions developed specifically for the study are asked at T2 and T3. These questions focused on the expectations of the participant and their opinion of the intervention program and treatment program at the TC.

## Data analysis

1. Differences between the intervention and control groups in categorical DVs (entry to the TC, TC stays of at least 30 days, 45 days and 90 days) will be analysed using binary logistic regression chi-square analysis.

2. Differences between the intervention and control groups in time spent at the TC will be analysed using Analysis of Variance, and Cox Proportionate Hazard Models.

3. Differences between the intervention and control groups in psychological outcomes over time (i.e., LSAS, BDI and BAI) will be explored using linear mixed modelling. In order to select the appropriate correlation structure for each of these DVs, linear models will initially be fitted using one of three possible correlation structures; compound symmetry (non-zero uniform correlations and uniform variance between time points), first order auto-regressive (observations closers in time are more highly correlated than observations further apart), and scaled identity (uniform variance across time with zero correlations between time points). The best fitting model for each outcome variable will be decided by selecting top fitting models based on Akaike’s Information Criterion (AIC).

4. Differences between the intervention and control groups in number of participants who no longer meet Mini criteria for SAD at the three month follow-up will be assessed using a 2 (intervention vs. control group) × 2 (SAD vs. no SAD) chi-square analysis. This analysis will only be conducted with participants who met Mini criteria for SAD at the baseline assessment (T1).

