## Research objectives

### Primary hypotheses

1. It is hypothesised that individuals in the intervention group will be more likely to enter the TC than individuals in the control group.

2. It is hypothesised that individuals in the intervention group will be more likely than individuals in the control group to stay in treatment for at least three months.

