#### Baseline assessment (T1)

Baseline assessments are administered using a standardised protocol. All researchers received prior training on the instruments used in the assessment prior to conducting interviews. In addition, new research officers conducted a number of practice assessments with a clinical psychologist at OHV prior to working with clients. The first assessment conducted by new research officers was also co-administered by a clinical psychologist at OHV, in order to ensure adherence to the assessment protocol, and to assess interrater agreement. Research officers are fully briefed as to the requirements associated with duty of care, and are made aware of the safety protocols outlined by OHV. Given the time commitment associated with the baseline (approximately 1 ½ - 2 hours) participants are reimbursed with a $25 retail voucher. For a list of measures used in the baseline assessment, see Table 1.

**Table 1 T1:** Measures administered at each assessment

**Measure**	**Baseline (T1)**	**Post intervention (T2)**	**Follow-up (T3)**
Demographic questions	✓	-	✓
TLFB	✓	-	✓
MINI	✓	-	✓^a^
ASSIST	✓	-	✓
LSAS	✓	✓	✓
BAI	✓	✓	✓
BDI	✓	✓	✓
CMR	✓	✓	-
CSQ-8	-	✓^b^	-

*Note.* TLFB = Timeline Follow-back Method, MINI = Mini International Neuropsychiatric Interview, ASSIST = Alcohol, Smoking and Substances Involvement Screening Test, LSAS = Liebowitz Social Anxiety Scale, BAI = Beck Anxiety Inventory, BDI = Beck Depression Inventory-II, CMR = Circumstances, Motivation and Readiness for Treatment Scale, CSQ-8 = Client Satisfaction Questionnaire-8.

^a^only modules F, I and J are administered. ^b^only administered to intervention clients.

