#### Randomisation

Following the baseline interview, an independent researcher randomises participants to either the intervention or control group. A permuted block randomisation procedure is utilised (e.g., Altman et al., 2001) whereby participants are allocated to the intervention or control group through the use of a randomly generated number. The permuted blocks are organised in groups of four (e.g., AABB, ABAB, BBAA) the details of which are not known by investigators involved with the administration of the trial. A random number sequence is generated which indicates the block of four conditions to be utilised for the following four cases. The use of the permuted block randomisation process ensures that intervention group numbers are balanced at the end of each block and is thus the recommended process in studies with smaller samples (i.e., n < 100).

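### Item 1 of the data analysis leaves the method for both primary outcomes ambiguous and, as written, uses no baseline information; a prespecified logistic model with baseline CMRS and LSAS would be a modest improvement

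*Protocol article*

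**What the plan says.** The two primary hypotheses are that "individuals in the intervention group will be more likely to enter the TC than individuals in the control group", and that the intervention group is more likely "to stay in treatment for at least three months". Data analysis, item 1, covers both. Its outcomes are "entry to the TC, TC stays of at least 30 days, 45 days and 90 days", and the method is given only as "will be analysed using binary logistic regression chi-square analysis". No covariate is listed, and nothing says that the analysis is unadjusted.

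Table 1 (Baseline assessment) schedules the LSAS at T1, T2 and T3. It schedules the CMRS at T1 and T2 under a shortened label, explained in the table note as "CMR = Circumstances, Motivation and Readiness for Treatment Scale". Allocation comes afterwards: "Following the baseline interview, an independent researcher randomises participants". The Randomisation section describes permuted blocks of four and states no stratification factor. The CMRS section says that the scale "was found to be predictive of treatment durations of longer than 30 days" and that items are answered "with the option to select N/A if the question does not apply to the respondent". The CMRS appears in no hypothesis and in no item of the data analysis.

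**The concern.** Item 1 is the only statement of how the primary binary outcomes will be compared, and it does not settle which analysis is primary. A contingency-table chi-square and a logistic regression can give different answers once covariates enter. A reader cannot tell whether baseline data are meant to be used, and the choice could be made after the results are seen.

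The trial also holds baseline measures that may bear on the outcome. The article cites the CMRS as predicting longer stays. Its Background argues that social anxiety hinders entry and retention, which makes baseline LSAS a plausible predictor on the trial's own rationale. Blocking balances numbers per arm, not readiness or severity. What is at stake is some power and a prespecified answer, not the validity of the comparison.

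**Working it through.** **Method wording.** Item 4 of the same section, on remission of SAD, spells out a two-by-two table for its chi-square test. Item 1 instead joins the names of two methods. It can be read as two separate analyses, or as the chi-square statistic of a logistic model. The text supports neither reading over the other.

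**Eligibility of the covariates.** T1 precedes randomisation, so T1 CMRS and T1 LSAS are proper baseline covariates. The T2 CMRS is measured after randomisation and is not. Any adjustment therefore has to name T1.

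**Prognostic evidence.** The cited CMRS result concerns stays above 30 days. It matches one of the four outcomes in item 1 and bears partly on the 90-day outcome, since anyone who leaves before 30 days also fails at 90. Nothing is cited on entry. No odds ratio, correlation or R² is given, so covariate strength below is assumed and shown as a range.

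**Size of the gain, closed form.** The plan has no figure of its own on this point. Its target of 146 is taken as given (73 per arm), with outcomes assumed known for all. Control rates are assumed, because none is stated.

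- Model: logit p(X) = a + ln(OR)·X, with X standard normal and a chosen so that the mean of p(X) equals the control rate p.
- R² = Var[p(X)] / [p(1 − p)]. Effective-size factor = 1/(1 − R²).
- Power = Φ[(d − 1.96·se₀)/se₁], with n = 73 × factor per arm. Here d is the difference in proportions, se₀ its pooled standard error and se₁ its unpooled standard error.
- Unadjusted, 50% vs 70%: se₀ = √(2 × .6 × .4/73) = .0811; se₁ = √((.25 + .21)/73) = .0794; Φ[(.20 − .1589)/.0794] = .698. The same formula for 20% vs 40% gives .756.

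| Assumed OR per SD | 50% vs 70%: R², factor, acts like N, power | 20% vs 40%: R², factor, acts like N, power |
|---|---|---|
| 1.25 | .012, 1.012, 148, .703 | .008, 1.008, 147, .759 |
| 1.5 | .038, 1.040, 152, .715 | .026, 1.026, 150, .767 |
| 2.0 | .098, 1.109, 162, .743 | .071, 1.076, 157, .787 |

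The gain is 0.3 to 0.5 points at 1.25, 1.1 to 1.7 at 1.5, and 3.1 to 4.5 at 2.0.

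**Size of the gain, simulation.** There were 4,000 trials per scenario, N = 146, 1:1, with logistic regression fitted with and without one standard-normal covariate. The assumed rates were 30 vs 53%, 40 vs 63% and 55 vs 77%. Simulation error in power is about 0.6 points.

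| OR per SD | Change in power (points) | Variance of standardised risk difference, adjusted/unadjusted |
|---|---|---|
| 1.25 | −0.7 to +1.2 | .990 to .999 |
| 1.5 | +0.3 to +1.4 | .966 to .976 |
| 2.0 | +1.7 to +4.1 | .916 to .931 |
| 2.5 | +4.4 to +5.6 | .838 to .891 |
| 3.0 | +5.7 to +7.5 | .815 to .846 |

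The two methods agree. The standard error of the log odds ratio moves the other way: for 40 vs 63% it rises from .343 unadjusted to .368 adjusted at an OR of 2.0. The adjusted odds ratio is conditional and lies further from 1. The benefit therefore shows as power, or as precision of a standardised risk difference, and not as a tighter odds ratio.

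**The case against.** The strongest reply is that this rests on silence. A condensed article commonly leaves the covariate list to the full protocol or SAP, which are not shown, and item 1 does name logistic regression. That stands as far as it goes. A reader might infer that the trial has decided against baseline adjustment; the text does not say so. What remains is a defect in the wording itself: the method for both primary outcomes is named in a way that could exclude covariates or admit them.

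Three other stronger readings are tempting and unsupported:

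- **That the CMRS is a strong predictor of the primary outcomes.** The article gives no strength, and the cited result is for stays above 30 days, not for entry or 90 days.
- **That entry and retention are the least powered outcomes in the trial.** No control rates are given, so no ranking can be derived. The SAD-remission comparison in item 4 uses only participants with SAD at baseline and needs a T3 interview.
- **That adjustment is free precision.** With a weak covariate the gain is close to nil, the log odds ratio has a larger standard error, the estimand changes unless results are standardised, and incomplete CMRS totals need a rule.

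It is also fair to say that an unadjusted test after randomisation keeps its type I error, and that its standard error already allows for chance imbalance. Adjustment here is an improvement, not a correction of an invalid analysis.

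**Conclusion.** The point holds in limited form. Item 1 leaves the primary method ambiguous and, as written, makes no use of baseline measures that the trial already collects before randomisation. For one covariate and 146 participants, adjusting is worth about 0 to 1.7 points of power at an odds ratio per SD of up to 1.5, and about 2 to 4.5 points at 2.0; for 20% vs 40%, power goes from .756 to about .787 at 2.0. Larger gains need stronger covariates than anything in the article supports. All of this rests on assumed covariate strength, assumed control rates and complete outcomes. No separate gain has been calculated for the LSAS. The change is worth making because it is cheap and fixes the analysis in advance, but its priority is low.

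**What to change.** Reword item 1 so that the primary analysis is binary logistic regression, in all randomised participants, of (a) entry and (b) having entered and stayed at least 90 days. The model terms are arm, T1 CMRS total and T1 LSAS total. Report the covariate-standardised risk difference with its 95% confidence interval as the effect measure, so that the result does not rest on a conditional odds ratio. Keep the unadjusted chi-square test as a sensitivity analysis.

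State a prorating rule for CMRS totals when items are marked not applicable.

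The cost is wording and a little programming for the standardisation. No new data, visits or participants are needed.

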## Background

Treatment engagement and retention in residential drug rehabilitation settings for individuals with substance misuse and psychiatric comorbidities is variable [1-4]. Studies have implicated mental health conditions such as social anxiety as having a negative impact on engagement and retention [5]. As residential drug rehabilitation is often the last resort for people with severe substance misuse problems, effective management of negative prognostic factors would be a significant contribution to improved treatment outcomes. In Australia, as elsewhere, residential drug treatment is generally provided by Therapeutic Communities (TC). TCs are intense psychosocial based interventions which are grounded in the assumption that substance misuse is a dysfunction of lifestyle and character development involving the whole person, resulting in a range of inter and intra personal difficulties, which are most effectively addressed in long term treatment in a community comprised of therapists and peers (i.e., other uses) [6,7]. Treatment in TCs involves clients moving through a number of treatment stages over a six to 15 month period. Each stage is associated with specific learning objectives, which facilitate transition to subsequent stages.

Individuals attending residential drug treatment generally present with increased severity of symptoms e.g., [8] and incidence of psychiatric co-morbidity e.g., [9] relative to outpatients, and are more likely to have significant social problems [10]. Unsurprisingly, individuals with co-occurring psychiatric disorders are at greater risk of poor treatment retention e.g., [11,12] than those without such comorbidities. Thus, given the complex nature of patients attending TCs, treatment dropout is high. For example, Polimeni, Moore and Gruenert [13] examined dropout rates from an Australian TC over a 10 year period and found that approximately 45% of patients dropped out of treatment in the first five weeks. Australian Institute of Health and Workforce Studies revealed that four percent of patients stay in residential treatment less than one day, and 40% less than one month [14]. This low rate of retention is mirrored in data collected in other Western countries [15,16].

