## Method/design

### Study design

The study design is a randomised control trial where the intervention is being compared to treatment as usual. Enrolment is conducted at Odyssey House Victoria (OHV), an addiction treatment facility located in Melbourne, Australia. Enrolment commenced June 2010 and is ongoing. All procedures are conducted in accordance with the Australian Code for the Responsible Conduct of Research and were approved by the Deakin University Human Research Ethics Committee.

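### ANOVA of time spent at the TC cannot represent unfinished stays or tell planned completion from premature exit

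*Protocol article*

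**What the plan says.** Item 2 of the Data analysis section states that group differences in "time spent at the TC will be analysed using Analysis of Variance, and Cox Proportionate Hazard Models". It gives no upper limit, event definition or censoring rule. Four other places bear on it:

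- **Program length.** The Background says of therapeutic communities in general: "Treatment in TCs involves clients moving through a number of treatment stages over a six to 15 month period".
- **Enrolment.** Under Study design: "Enrolment commenced June 2010 and is ongoing".
- **Last scheduled contact.** Under Follow up assessment (T3): "Three months after entering the TC, all intervention and control group participants are asked to complete a follow up interview". For people who do not enter, "the T3 is administered six months after the baseline assessment".
- **The question asked.** Primary hypothesis 2 is that "individuals in the intervention group will be more likely than individuals in the control group to stay in treatment for at least three months". Item 1 of the Data analysis section handles this through binary outcomes: "entry to the TC, TC stays of at least 30 days, 45 days and 90 days".

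**The concern.** ANOVA compares means of values that are taken as complete, and it has no means of marking a stay as still running. Where programs can last up to 15 months, recruitment is staggered and the scheduled visits end three months after entry, some entrants may still be resident when the data are analysed. ANOVA would record their days so far as if they had left that day. If the intervention improves retention, more people are still resident in that arm, so more of its stay is cut off and the difference in total stay shrinks.

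ANOVA of raw days also ignores why a stay ended. As an illustration with 30-day months, someone who completes a six-month program scores about 180 days. Someone who leaves a 15-month program early, in month ten, scores about 300. The analysis rates the premature exit 120 days better than the completion, although the trial's aim is to reduce premature dropout.

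At stake is a named supporting analysis for hypothesis 2. It could understate a real benefit, or seem to disagree with the 90-day result for reasons unrelated to dropout.

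**Working it through.** The article attaches no figure to the time analysis, so there is none to reproduce. The check asks how far unfinished stays could move each of the two named methods.

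**Input from the document.** About 45% of patients left an Australian TC within five weeks (Background), so the share remaining at day 35 is 0.55.

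**Assumptions not in the document.** Dropout hazard ratio 0.60; planned completion uniform on 180 to 450 days (6 to 15 months of 30 days); 60 entrants per arm; 300 simulated trials per scenario. Three data cuts: uniform 90 to 365 days after entry, everyone cut at day 90, and complete follow-up.

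**Dropout curve.** Share not yet dropped out at day t = 0.55^(HR × (t/35)^k), with k = 1 (constant hazard) or k = 0.6 (hazard falling over time). At day 90, 90/35 = 2.571:

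- k = 1: control 0.55^2.571 = 0.215; intervention 0.55^(0.60 × 2.571) = 0.398.
- k = 0.6: 2.571^0.6 = 1.762; control 0.55^1.762 = 0.349; intervention 0.55^(0.60 × 1.762) = 0.531.

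On these assumptions 21% to 35% of control entrants and 40% to 53% of intervention entrants are still resident at day 90. The arm that benefits has more stay left to lose.

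**ANOVA: difference in mean days, intervention minus control**

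| Data cut | k | Full stay | Days observed |
|---|---|---|---|
| 90–365 days | 1 | 33.4 | 26.9 |
| 90–365 days | 0.6 | 52.5 | 35.8 |
| All at day 90 | 1 | 34.6 | 13.2 |
| All at day 90 | 0.6 | 51.1 | 12.6 |
| Complete follow-up | 1 | 34.1 | 34.1 |
| Complete follow-up | 0.6 | 50.0 | 50.0 |

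With the spread-out cut, the shrinkage is 1 − 26.9/33.4 = 19% or 1 − 35.8/52.5 = 32%. The day-90 rows are a correct comparison of days within the first 90. They mislead only if read as total stay, so they are not a measure of bias in that narrower quantity. With complete follow-up the censoring problem disappears.

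**Cox: estimated hazard ratio (assumed true value 0.60), range over the same six scenarios**

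| How the end of a stay is coded | Hazard ratio |
|---|---|
| Premature exit is the event, others censored, no time limit | 0.59–0.61 |
| Same, limited to 90 days | 0.59–0.61 |
| Planned completion also counted as an event | 0.59–0.66 |

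The Cox model recovers the assumed effect with or without a 90-day limit, provided that residents and completers are censored. The problem therefore lies with the ANOVA.

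**The case against.** Several arguments limit this point.

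**The Cox model.** A reader might infer that residents still in treatment and planned completers are counted as dropouts in the Cox model. The document does not say so. It states no event or censoring rule, Cox regression exists to handle unfinished stays, and an article commonly leaves that rule to the full protocol or analysis plan. This argument stands: the Cox model is not wrong as written.

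**A 90-day limit.** A reader might also infer that the absence of a 90-day limit is itself the error. It is not. Correctly censored Cox gives the same answer with or without the limit. Total tenure is a legitimate outcome too: the Background calls it a significant predictor of treatment outcome, and the Discussion cites evidence that time in treatment correlates with outcome only after three months.

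**Hypothesis 2.** The binary outcomes in item 1, including the 90-day stay, do not depend on program length or on how later stays end. They are unaffected.

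**The premises.** The 6 to 15 months describe TCs in general, and the site's own program length is not given. T3 is an interview, and nothing says that length of stay is recorded only up to T3; it may come from site records. If the analysis waited until every entrant had left, ANOVA would face no censoring. All this makes the size uncertain. It does not remove the point, because the document does not commit to waiting, and complete records would still leave planned completion and premature exit undistinguished.

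**Conclusion.** The point holds in a narrow form. The text commits to ANOVA for time spent at the TC. If any entrant is still resident at analysis, ANOVA takes the days so far as the completed stay. Whether or not stays are complete, it cannot separate planned completion from premature exit. The between-group difference in total stay can be understated, by 19% to 32% in the scenarios with a data cut 90 to 365 days after entry and by nothing from censoring if all stays are complete. Those percentages rest on the assumed hazard ratio, completion times and data cut; they illustrate direction and rough size and do not forecast this trial.

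The fault is in one of two methods named for a supporting outcome. It does not reach the Cox model or the binary retention analyses. It is worth correcting because the change is cheap and no censoring rule added elsewhere could make an ANOVA of raw days suitable for unfinished stays.

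**What to change.** Drop the ANOVA of raw days and make the Cox model the analysis of time at the TC. Define premature exit as the event, and censor residents still in treatment at the data cut and people who complete the program as planned.

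If a comparison of means is also wanted, compare days in the TC over the first 90 days (the smaller of the stay and 90) and label it as that quantity, not as total stay. It is observable for every entrant followed for three months and uses the trial's own retention threshold. Limiting the Cox model to 90 days as well is an option, not a requirement.

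**Cost.** The change affects analysis wording only, although the reason for leaving must be available to separate completion from premature exit. Under the 90-day mean, stay beyond day 90 is left to the Cox model or to description. Power may also be lower if the effect continues after day 90. In a simulation of 4,000 runs (assumed 35% v 55% reaching day 90, 60 entrants per arm), power for raw days against days limited to 90 was about 59% v 57% with a later hazard ratio of 0.75, and about 67% v 56% with 0.57. The reason for the change is therefore bias and interpretability, not power.

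### The LSAS, BDI and BAI mixed models are confined to three covariance structures that suit the uneven visits poorly; an unstructured covariance should be prespecified instead

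*Protocol article*

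**What the plan says.** Item 3 of the Data analysis section of the protocol article states that "psychological outcomes over time (i.e., LSAS, BDI and BAI) will be explored using linear mixed modelling". It then closes the list of covariance models: "linear models will initially be fitted using one of three possible correlation structures". The three are:

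- A structure with one variance and one shared correlation, worded as "compound symmetry (non-zero uniform correlations and uniform variance between time points".
- A structure for which only the correlation is described, and not the variance: "observations closers in time are more highly correlated than observations further apart". This is AR(1).
- A structure with no within-person correlation at all, worded as "scaled identity (uniform variance across time with zero correlations between time points".

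The choice is made separately for each outcome: "The best fitting model for each outcome variable will be decided by selecting top fitting models based on" AIC. Unstructured and heterogeneous-variance forms are not candidates, and no robust standard error is mentioned.

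There are three assessments. Under Post intervention assessment (T2), the second falls at the end of the fourth session in the intervention arm and six weeks after baseline in the control arm. Under Follow up assessment (T3), the third falls three months after entry to the therapeutic community. For those who never enter, "the T3 is administered six months after the baseline assessment".

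**The concern.** AIC can only rank the models it is offered. If all three are wrong for these data, the rule returns the least wrong one, and its model-based standard errors carry the misfit.

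Two restrictions matter here.

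- **Equal variance.** It is stated for compound symmetry and scaled identity. For AR(1) only the correlation is described, so equal variance there is inferred from the standard form.
- **Correlation pattern.** Compound symmetry gives all three pairs of visits one correlation. AR(1) by visit order makes the T1-T2 and T2-T3 correlations equal. For a control participant who never enters treatment, the first gap is six weeks and the second about 20 weeks (26 less 6). For entrants the second gap depends on the date of entry.

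The secondary hypotheses on social anxiety severity (1) and on anxiety and depression symptoms (3) rest on these models. A standard error that is too large loses power, and one that is too small raises the false-positive rate. The same fitted model can do the first for one contrast and the second for another.

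**Working it through.** The protocol has no figure of its own to reproduce on this point. It gives no SDs or correlations for LSAS, BDI or BAI, so every covariance input below is an assumption.

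**Step 1. Assumed truth.** Correlations are .7 (T1-T2), .5 (T2-T3) and .35 (T1-T3). SDs are either equal (set to 1) or 20/25/28 at T1/T2/T3. Data are complete, with N = 121 from the Power analysis section.

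**Step 2. What AIC would choose.** Each candidate is fitted to the assumed covariance by Gaussian likelihood, and the AICs are compared at N = 121.

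| | Compound symmetry minus AR(1) | Scaled identity minus AR(1) | AR(1) minus unstructured |
|---|---|---|---|
| Equal SDs | 17.9 | 106.0 | 0.3 |
| SDs 20/25/28 | 15.0 | 95.2 | 24.6 |

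AR(1) is therefore chosen from the list of three in both cases. With unequal SDs an unstructured matrix would beat it clearly. With equal SDs the two are about level.

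**Step 3. Standard errors under the chosen AR(1).** The sample-size factor cancels, so the ratio of model to true standard error is the square root of (model variance of the contrast / true variance of the contrast). Type I error at a nominal two-sided .05 is 2 × (1 − Φ(1.96 × ratio)).

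*Equal SDs.* The fitted AR(1) has correlation .60.
- T2-T1: model 2(1 − .60) = .80; true 2(1 − .70) = .60; ratio √(.80/.60) = 1.155; type I error .024.
- T3-T1: model 2(1 − .36) = 1.28; true 2(1 − .35) = 1.30; ratio .992; type I error .052.

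*SDs 20/25/28.* The fitted AR(1) has variance 600.3 and correlation .571.
- T2-T1: model 2 × 600.3 × (1 − .571) ≈ 514.7 (unrounded correlation); true 400 + 625 − 2 × .7 × 500 = 325; ratio √(514.7/325) = 1.258; type I error .014.
- T3-T1: model 808.8; true 400 + 784 − 2 × .35 × 560 = 792; ratio 1.011; type I error .048.
- T3 between arms: model 600.3; true 784; ratio √(600.3/784) = .875; type I error .086.

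**Step 4. Power at T2-T1.** A contrast with true power of 80% keeps Φ(1.96 + .84 − 1.96 × ratio). This is about 70% at a ratio of 1.155 and 63% at 1.258.

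**Step 5. Simulation of the planned rule.** N = 146, 21% monotone loss completely at random, REML, and AIC choice among the three structures; 1000 runs per scenario. Cells give type I error, with the ratio of mean model to empirical standard error in brackets. SDs are for T1/T2/T3 and correlations for T1-T2/T1-T3/T2-T3.

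| Assumed truth | T2-T1 | T3-T1 | T3 between arms |
|---|---|---|---|
| SDs 1/1.2/1.4, r .7/.4/.5 | 1.6% (1.25) | 5.8% (0.97) | 9.0% (0.84) |
| SDs 1/1.1/1.2, r .7/.5/.6 | 3.3% (1.08) | 4.8% (0.99) | 7.4% (0.89) |
| Equal SDs, r .8/.4/.5 | 1.3% (1.31) | 6.5% (0.94) | 4.2% (1.02) |
| SDs 1/.9/.75, r .7/.5/.6 | 4.1% (1.03) | 3.6% (1.06) | 2.5% (1.18) |

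A fifth scenario, true compound symmetry with r = .6, gave 4.5% to 5.6% (0.97 to 0.99), which is no harm. An unstructured covariance gave 4.4% to 5.8% (0.96 to 1.03) across all five. It also had the lower AIC in 88% to 100% of runs in the four scenarios tabulated. Monte Carlo error is about 0.7 percentage points at a 5% rate.

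**The case against.** The strongest reply is that AIC choice among named structures is itself a prespecified rule, and that the size of the harm rests wholly on assumed covariances. Both points stand. They limit the size of the problem, but they do not justify leaving an affordable structure off the list.

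The article also does not say whether random effects accompany these structures. A random intercept with scaled-identity residuals is compound symmetry. One with AR(1) residuals loosens the T1-T3 correlation. Neither lifts equal variance or the equality of the T1-T2 and T2-T3 correlations, so the objection narrows the point without removing it. Likewise, an AR(1) defined on actual dates would ease the spacing problem, but the article does not describe one.

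Four stronger readings are tempting and are not supported.

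- **False positives at T3-T1.** Under the assumed correlations, compound symmetry would understate this standard error (type I error .091, or .086 with SDs 20/25/28). AIC would not choose compound symmetry there, and under AR(1) the contrast is about right.
- **Scaled identity as a live danger.** A reader might infer that the trial could analyse three scores from one person as independent. In the calculation its AIC was worse than the best candidate by about 95 or more, and it was never selected in 5000 simulated runs. It is a poor candidate that AIC would in practice reject.
- **Baseline LSAS spread narrowed by selection.** The inclusion criterion asks for one moderate symptom and avoidance of one situation on a 24-item scale. That is a low bar, and nobody is selected on BDI or BAI. Unequal variance is possible but does not follow from the entry rule.
- **Arm-by-time contrasts settling secondary hypothesis 1.** That hypothesis is worded as a reduction from T1 to T2 within the intervention group. The T2-T1 ratios above carry over to a within-arm change if both arms share the covariance, but there the error under the stated assumptions is conservative.

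**Conclusion.** The point holds at moderate size and for secondary outcomes only. The article fixes a closed list that omits the one structure able to fit three unevenly spaced visits without restriction.

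Under correlations .7/.5/.35 and the AIC rule as written, the T2-T1 standard error is about 16% too large with equal SDs and 26% too large with SDs 20/25/28. The T3 between-arm standard error is about 12% too small only if the SDs rise in that way. In the wider simulation the AIC-chosen model gave type I errors from 1.3% to 9.0%. All of this depends on assumed SDs and correlations, and it vanishes near compound symmetry. Nothing here touches the primary hypotheses on entry and on staying three months, which are not analysed with these models.

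**What to change.** In item 3 of Data analysis, replace the selection step with one prespecified model for each of LSAS, BDI and BAI: arm, time and arm-by-time, with an unstructured covariance over T1, T2 and T3, fitted by REML with Kenward-Roger degrees of freedom. State a fallback, either heterogeneous compound symmetry or robust standard errors, to be used only if that model does not converge. Delete scaled identity and the AIC choice.

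The cost is analysis wording only. An unstructured matrix for three visits has six parameters, against two for compound symmetry or AR(1), so at most four more. The target sample of 146 supports that easily, and little precision is lost if compound symmetry turns out to be true. The change also removes a data-driven choice made separately for three outcomes.
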